#### **8.3. Procedures for eliciting reports of and for recording and reporting adverse event and intercurrent illnesses**

All adverse events, including intercurrent illnesses and an increase in severity or frequency of a sign/symptom of a concomitant disease will be reported on and documented.

Unanticipated adverse events are to be documented on an "Adverse Event (AE) / Serious Adverse Event (SAE)" page of the case report form. All findings in patients experiencing unanticipated adverse events must be reported there and in the patient's medical records.

The investigator should state whether the event is considered as serious, if a causal relationship to trial therapy exists, and note the severity of the event.

The severity of adverse events has to be classified as:

- o mild = normal activities of daily life can be performed
- o moderate = normal activities of daily life are restricted
- o severe = normal activities of daily life cannot be performed

For all SAEs - independent of a possible causal relationship - the investigator will submit a SAE report to the recipient (coordinating investigator) indicated on the cover page of the form **within 24 hours** after having gained knowledge of the event. The investigator is obliged to provide a complete documentation of the course and the measures taken, if necessary with the submission of original findings.

In addition, any SAE will be registered in the "Adverse Event Form" of the CRF.

After receipt of the initial report, the coordinating investigator will review the information and contact the investigator if necessary, to obtain further information for assessment of the event.

The investigator will submit, if necessary, copies of all these reports to the independent ethics committee concerned.

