**8. Assessment of Safety**

**8.1. Specification of safety parameters.**

All complications and unanticipated adverse events will be reviewed by the coordinating investigator. The coordinating investigator is responsible for identifying issues that warrant immediate action and the evaluation of trends of consequence.

For the purposes of this study we will define adverse and serious adverse events according to the ICH-GCP guidelines (guidelines for Good Clinical Practice; ICH-Harmonised Tripartite Guideline; EMEA Status as of June 1996) as follows:

Adverse Event (AE): Any untoward medical occurrence in a patient or clinical investigation subject which does not necessarily have a causal relationship with this treatment. An adverse event (AE) can therefore be any unfavourable and unintended sign (including an

abnormal laboratory finding), symptom, or disease temporarily associated with the treatment investigated in the study, whether or not related to the treatment product.

In PISO, AEs are likely to occur with medium to high frequency, as the population studied is defined by frequent and frequently changing somatic symptom complaints. It is up to the investigator at the respective trial site to decide whether complaints of the patients are to be seen as anticipated in this sense or whether they are judged as being unanticipated and hence necessitate immediate information of the coordinating investigator.

Serious adverse event (SAE): Any untoward medical occurrence that:

- results in death,
- is life-threatening,
- requires inpatient hospitalisation or prolongation of existing hospitalisation,
- results in persistent or significant disability/incapacity
- congenital anomaly or birth defect.

In PISO, increased depressivity and/ or suicidality is considered as SAE and should be reported in the same way.

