### **Management of „re-somatization“**

During the course of a therapy, it happens almost regularly that distinctively somatoform patients increasingly complain about their symptoms and the feared organic reasons thereof, and all insights into the situative and affective contexts seem to be lost. In this situation, it is important to accept this re-somatized offer as currently necessary for the patient and not to confront the patient with the seemingly lost insights, and at worst in a disappointed and reproachful way. When the therapist maintains an accepting attitude, the patient will sooner be able to use these insights again.

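### Section 8.3 promises that all adverse events are documented but names a CRF page only for unanticipated events and SAEs, so non-serious worsening of bodily symptoms can be missing from the adverse-event data

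*Protocol*

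**What the plan says.** Section 8.1 of the protocol adopts the ICH-GCP definition, under which an adverse event can be any unfavourable sign, "symptom, or disease temporarily associated with the treatment investigated in the study", whether or not related. It expects such events to be common because "the population studied is defined by frequent and frequently changing somatic symptom complaints". It then sets the rule: "It is up to the investigator at the respective trial site to decide whether complaints of the patients are to be seen as anticipated" or as unanticipated, the latter calling for prompt notification of the coordinating investigator. No criteria are given. On central review it says "All complications and unanticipated adverse events will be reviewed by the coordinating investigator", and it makes the same person responsible for evaluating trends.

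Section 8.3 opens with the general rule, which is to document every event: "All adverse events, including intercurrent illnesses and an increase in severity or frequency of a sign/symptom of a concomitant disease will be reported on". The next sentence is narrower: "Unanticipated adverse events are to be documented on an" AE/SAE page of the CRF. The one after it attaches the reporting duty to the same subset: "All findings in patients experiencing unanticipated adverse events must be reported there" and in the medical records. Section 8.3 also asks for seriousness, causality and severity. Every SAE is reported within 24 hours whatever its cause and is also entered in the CRF. Section 8.1 treats increased depressivity or suicidality as an SAE.

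Section 8.2 places the assessment of bodily complaints in the 12 treatment sessions of the experimental arm and the 3 case management sessions of the control arm. Safety parameters are recorded again at 3 months and 1 year.

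**The concern.** The general rule and the CRF rule do not have the same scope. A site reading section 8.3 cannot tell whether an anticipated, non-serious event needs a CRF entry, and if so where. The events at issue are the ones this population produces most readily: more pain, or new bodily complaints.

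Three features could make the omission uneven. The classification has no criteria and may vary by site. Staff who treat the patients know the arm. The treatment manual (Supplement 3a, on re-somatization) tells therapists in the experimental arm that "it happens almost regularly that distinctively somatoform patients increasingly complain about their symptoms", which may make such complaints look expected there.

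At stake is the credibility of the non-serious safety comparison. An event that was never entered cannot be recovered by any analysis plan.

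**Working it through.** The protocol gives no figure to reproduce, so the check sets the rules side by side and follows an event through them.

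**1. Route of each kind of event**

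| Event | Documented under the general rule of 8.3? | CRF page named? | Route to the coordinating investigator |
|---|---|---|---|
| SAE, including increased depressivity/suicidality | Yes | Yes | Report within 24 hours |
| Non-serious, unanticipated | Yes | Yes | Notification and review under 8.1 |
| Non-serious, anticipated | Yes | None named | None named, unless it counts as a complication |

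The third row is the gap. Worsening of the index complaint belongs to the general rule because the definition in 8.1 covers any unfavourable symptom. The example in 8.3 speaks of a concomitant disease, but it only illustrates a sentence about all adverse events.

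**2. Who decides.** The site investigator does (8.1). Section 4.8 says that patients and treating staff are not blinded. Section 4.3 provides blinded assessors and asks patients to withhold treatment details from investigators, but nothing in section 8 requires the classification to be made blind. Complaints raised in sessions are first heard by staff who know the arm.

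**3. Opportunity to report.** Contacts at which complaints are assessed (8.2): 12 versus 3, and 12 / 3 = 4. The experimental arm has four times as many scheduled occasions.

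**4. What a filter does to the counts.** Let r be the true rate of non-serious worsening in an arm, f the share that sites call anticipated and do not enter, and n = 88 the planned number per group.

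- Entered events per arm = n × r × (1 − f).
- Ratio between arms = (r1 / r2) × (1 − f1) / (1 − f2).
- If f1 = f2, the ratio is preserved and only the absolute counts shrink. If f differs by arm, the ratio is distorted by (1 − f1) / (1 − f2).

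The protocol gives no value for r or f, so no numerical size follows.

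**5. What else would show the worsening.** SOMS-7 and SF-36 are measured at t0, t1 and t2 (4.1). Taking SOMS-7 to look back seven days and t1 to be the 3-month assessment, one measurement covers about 7 of the 12 × 7 = 84 treatment days, or 7 / 84 = 8%. A transient worsening earlier in treatment could be missed. Neither scale carries the seriousness, causality and severity judgements of 8.3. The safety parameters recorded at 3 months and 1 year (8.2) have no named form. Therapist notes and audiotapes exist for sessions but are not described as a trial dataset.

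**6. Monitoring.** Section 11.2 lists eligibility, consent and outcome variables for 100% monitoring. Adverse events are not on that list, so under-entry is less likely to be noticed.

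**The case against.** The best defence is that the sentences are compatible: everything is documented somewhere, and a dedicated page serves a subset that needs quick action. Section 8.1 does give the distinction that notification role. The CRF is not shown and may hold a field for anticipated events. This makes the defect one of unclear instruction rather than a proven exclusion. It does not remove the defect, because the protocol names no place for these events.

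The defence is right on several further points. A reader might infer that only unanticipated events ever reach the CRF or the coordinating investigator. That is not so, since every SAE does, including hospitalisation and lasting disability. A reader might infer that symptom worsening disappears from the trial's data. It does not: SOMS-7 and SF-36 are self-reported, need no anticipated/unanticipated judgement and are analysed by randomised arm (9.7). The particular risk that the protocol names (2.3 and 12), depressive or suicidal change, is classed as an SAE and so escapes the filter. The re-somatization text guides the therapist's response. It sets no adverse-event rule and does not establish that clear worsening would be called anticipated.

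It is also fair to object that putting every complaint on an AE page would carry the 12 to 3 imbalance in contacts into the raw counts. That objection stands, and the fix has to deal with it.

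**Conclusion.** The point holds for non-serious events. The passages conflict in scope, the classification has no criteria, and non-serious worsening of bodily symptoms can be absent from the adverse-event data, possibly differently by arm and site. The coordinating investigator's trend review would share that gap, apart from SAEs and complications.

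The size is unknown. Any figure for missing events or for a spurious difference between arms would rest on invented rates. The documents do not show that differential filtering will occur, only that nothing prevents it. They do not support a claim that serious harm goes unrecorded.

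The conclusion assumes that sites would follow the protocol text as written and that no other instruction, such as the CRF itself, already requires anticipated events to be entered. The change should be made, because it is cheap and the data cannot be recovered later.

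**What to change.** Reconcile sections 8.1 and 8.3 as follows.

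- In 8.3, require every adverse event in both arms to be entered on the AE/SAE page, with seriousness, causality and severity.
- Make anticipated/unanticipated a field on that page. Use it only to trigger prompt notification of the coordinating investigator, never as a condition for recording.
- In 8.1, extend the coordinating investigator's trend review to all recorded adverse events. Leave the 24-hour SAE route as it is.
- In 8.2, state that adverse events are elicited in the same way in both arms at the 3-month and 1-year assessments. Base the between-arm comparison of non-serious events on those, and list events reported in sessions separately, because of the 12 versus 3 contacts.

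The cost is wording in three sections and one CRF field. The downside is more AE pages per patient in a population with frequent complaints. Treatment and sample size are unaffected.

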#### **8.4. Type and duration of the follow-up of subjects after adverse events**

If required, a follow-up report including all new information obtained on the serious adverse event will be prepared and sent to the address of the SAE-form recipient or it will be collected by the monitor. The report should be marked "Follow-up report". If a SAE makes it necessary to initiate inpatient treatment, i.e. on a psychiatric ward due to acute suicidality, discharge information will be collected and treated as a further follow-up report.

## 9. Statistics

### 9.1. Description of the statistical methods to be employed

The data will be listed per center, per setting and per patient. Descriptive statistics will be calculated for each treatment group. Demographic and baseline data will be compared using appropriate statistical techniques.

For confirmatory analysis a modeling approach will be applied. The null hypothesis tested is: no treatment difference between control and intervention group with respect to the primary endpoint. A linear model with mixed effect will be used:

$$y_{i,j,c,s(c)} = \mu + \alpha_j + \eta_c + \zeta_{c,s(c)} + \varepsilon_{i,j,c,s(c)},$$

where  $y_{i,j,c,s(c)}$  is the response of individual  $i$  ( $i=1, \dots, m_{c,s}$ ) randomized to treatment  $j$  ( $j=1, 2$ ) for center  $c$  ( $c=1, \dots, C$ ) and setting  $s(c)$  ( $s(c)=1, \dots, n_c$ ). The notation indicates two treatment assign, and two level of stratification (patients within settings and settings within centers) with number of settings varying within centers. The total number of observations per treatment group is  $\sum_c \sum_s m_{c,s}$ .

The fixed-effects parameters in the model are  $\mu$  (the grand mean) and  $\alpha$  (the group effects). The random effect  $\eta$  indicates center effect,  $\zeta$  setting effect and  $\varepsilon$  measurement error. These three random variables will be assume statistically independent each other, with mean zero and component of variances  $\tau_\eta$ ,  $\tau_\zeta$ , and  $\tau_\varepsilon$  respectively.

The parameters of interest in this analysis are the mean of the control group  $\mu + \alpha_1$  and the contrast of means  $\alpha_1 - \alpha_2$  (which indicates treatment effect).

Estimation of model parameters will be calculated with REML (restricted maximum likelihood) method. Treatment effect will be tested with a likelihood ratio test (LRT at the alpha-level of 0.05). Additionally, centers and settings effect will be predicted with the best linear unbiased predictors (BLUPs) of the random effects. Asymptotic confidence intervals will be reported for all parameters in the model.

Distributional assumptions will be assessed (e.g. residual analysis) and transformation on the response variable will be done if it is necessary. Additionally, if adjustments for covariates are necessary they will be included in the model.

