### 9.2. The number of subjects planned to be enrolled

Sample size calculation is motivated by the primary endpoint, based on the Physical Component Summary of SF-36 (PCS). We assessed the PCS for somatoform disorders in the general population with a mean value of 45,76 (SD=10.03) (Schmitz and Kruse, German National Health Interview and Examination Survey - Mental Health Supplement (GHS-MHS) 1998, public use file) and, clinically more realistically, with 37 (SD=12.5) in a sample of 186 patients in the University Hospital Heidelberg, treated in the outpatient departments for psychosomatics and orthopaedic chronic pain, comparable to the trial criteria (Henningesen et al. 2005).

In the trial an effect size of 0.5 is assumed, which is based on the following considerations: Clinically important change on the SF-36 PCS (ie what patients regard as important change) has been considered as follows: small change= 2.5; moderate = 4.5 and large = 6.5 (Wiebe et al 2002). In a previous trial of PIT in a functional somatic disorder (Creed et al. 2003), patients who received PIT improved by a mean of 5.5 points on the PCS compared to those receiving usual care, and this was associated with a reduction of median number of days of restricted activity per month from 5 to 0. Therefore, assuming an effect size of 0.50 on the basis of a standard deviation of 12.5 implies a clinically significant, large change of 6.25 in this measure of physical quality of life.

A sample size of 63 in each group will have 80% power to detect an effect size of 0.50 assuming a mean value of 37 in the control group and a known common standard deviation of 12.5 using a two group normal test with a 0.05 two-sided significance level.

This sample size calculation is based on the standard statistic

$$n = 2\sigma^2 / \theta^2 (z_{0.8} - z_{0.025})^2 \approx 63,$$

where  $\sigma^2 = 12.5^2$ ,  $\theta = 6.25$ ,  $z_{0.8} = 0.84$ ,  $z_{0.025} = -1.96$  and effect size is  $\theta/\sigma$ .

Several scenarios are considered for the number of patients per group. Table 1 shows a deterministic sensitivity analysis for different values of effect size. On the bases of the above requirements the sample size of  $n = 63$  per group was determined. Although, the sample size is very sensible to possible changes of effect size.

**Table 1.** Sample size estimation per group for different effect size and power ( $\alpha = 0.05$ , 2-sided).

| effect size | power 70% | power 80% | power 90% |

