|-------------|-----------|-----------|-----------|
| 0.6         | 34        | 43        | 58        |
| 0.55        | 40        | 52        | 70        |
| 0.50        | 49        | 63 | 84        |
| 0.45        | 61        | 78        | 103       |
| 0.40        | 77        | 98        | 131       |

In order to assess if the trial could be underpowered, a further probabilistic sensitivity analysis on the sample size and the power is carried out. This analysis puts uncertainty over the parameters  $\theta$  and  $\sigma^2$ . It is assumed that the prior mean of  $\theta$  is 6.25 with standard deviation 1, while for  $\sigma$  is assumed a prior mean of 12.5 and standard deviation of 1 (subject to the constraint of  $\sigma$  to be positive).

A Monte Carlo simulation method is applied to simulate values of  $\theta$  and  $\sigma^2$  from their prior distributions, substituting them into the sample-size formula and the resulted simulation values  $n_1^*, \dots, n_B^*$  recorded.

For a fixed  $n$ , the power is given by

$$power = \Phi(\sqrt{(n\theta/2\sigma^2)} + z_{0.025}).$$

If is decided to use 63 patients per group, values for the  $power$  can be simulated using the same methodology, resulting in simulated values  $power_1^* \dots power_B^*$ .

A total of  $B=10000$  simulated values  $n_b^*$  and  $power_b^*$  were carried out. Figure 1 gives the density estimation of these two quantities. They present a clear uncertainty for sample size and power values.

To achieve a fixed power of 80 % the median of the simulated sample size  $n^*$  is 88. For a fixed  $n=63$  the median of the simulated  $power^*$  values is 65%. These results indicates that the deterministic sample size calculation may give optimistic results and a larger sample size should be used to achieve a power of 80%.

Fixing  $n=88$  in the power formula and simulating again  $B=10000$  gives a median power of 79.6 %, which is more close to the trial power requirements. The recommended sample size for this trial is  $n=88$  per group.

**Figure 1.** *Left panel:* distribution for necessary sample size  $n$  to achieve 80% power. *Right panel:* power distribution with a fixed  $n = 63$  patients per group.

[figure not shown][figure not shown]

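### The primary test pairs REML estimation with a likelihood ratio test of a fixed effect and names no other likelihood; read literally, it does not hold the 5% level

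*Protocol*

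**What the plan says.** Protocol section 9.1 sets out the confirmatory analysis as a linear mixed model with random centre and setting effects. On the hypothesis it says: "The null hypothesis tested is: no treatment difference between control and intervention group with respect to the primary endpoint".

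Treatment is not random in this model: "The fixed-effects parameters in the model are" the grand mean and the group effects alpha. The estimator is then named: "Estimation of model parameters will be calculated with REML (restricted maximum likelihood) method". The next sentence gives the test: "Treatment effect will be tested with a likelihood ratio test (LRT at the alpha-level of 0.05".

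No refit by full ML is mentioned, and no Wald, t or F test. The section asks for asymptotic confidence intervals for every parameter. It allows the response to be transformed. It does not say how treatment is coded.

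Section 9.2 supplies the planning values: "assuming an effect size of 0.50 on the basis of a standard deviation of 12.5 implies a clinically significant, large change of 6.25", tested "using a two group normal test with a 0.05 two-sided significance level". After a Monte Carlo exercise it recommends 88 per group.

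**The concern.** A likelihood ratio test of alpha compares the model that contains the treatment column with the model that lacks it. The restricted log-likelihood contains a term in log|X'V^-1X| and a constant (N - p) log(2*pi), where X is the fixed-effects design matrix and p its number of columns. Both change when the treatment column is dropped, so the two restricted likelihoods are not on a common footing. Twice their difference is displaced from chi-square(1) by an amount unrelated to the evidence for a treatment effect.

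This is the only confirmatory test of the primary hypothesis. If it is run as the two adjacent sentences read, its type I error is set by coding and units, which should have no influence on a p-value.

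**Working it through.** **Inputs.** From section 9.2: SD 12.5, difference 6.25, two-sided 0.05, 88 per group, so N = 176. From section 4.8: 1:1 allocation, stratified by hospital and setting. Centre and setting variances are not in the documents. They are assumed to be 0% each, then 5% each, of the total variance.

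**The plan's own figure.** n = 2 x 12.5^2 / 6.25^2 x (0.84 + 1.96)^2 = 2 x 4 x 7.84 = 62.7, so 63 per group as stated, with power 0.801. The planning inputs are therefore read as the protocol intends.

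**Displacement of the statistic.** Under the null, with no centre or setting variance,

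REML-based LRT ≈ chi-square(1) + shift, where shift = log(2*pi) - log(N v / SD^2).

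Here v is the variance of the treatment code: 0.25 for 0/1 and 1 for -1/+1. The size is P(chi-square(1) > 3.841 - shift), and log(2*pi) = 1.838.

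| Case (N = 176) | N v / SD^2 | Shift | Size |
|---|---|---|---|
| 0/1 coding, PCS points | 44 / 156.25 = 0.282 | 1.838 + 1.267 = 3.105 | 0.391 |
| -1/+1 coding, PCS points | 176 / 156.25 = 1.126 | 1.838 - 0.119 = 1.719 | 0.145 |
| 0/1 coding, 2*pi constant dropped | 0.282 | 1.267 | 0.11 |
| 0/1 coding, outcome in SD units | 44 / 1 = 44 | 1.838 - 3.784 = -1.946 | 0.016 |

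The first two rows are the same model, with the same data and the same fitted difference between arms. Their statistics differ by log 4 = 1.386 because of coding alone. Moving from points to SD units shifts the statistic by log(156.25) = 5.051.

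**Simulation.** The section 9.1 model was simulated under the null, with 10,000 trials per scenario, 6 centres and 9 centre-settings counted from the pilot table in section 9.3, and 1:1 allocation within setting. The restricted-likelihood LRT rejected as follows:

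- N = 176, 0/1 coding, no centre or setting variance: 0.391.
- N = 176, 0/1 coding, 5% each: 0.359 (0.355 with unequal setting sizes).
- N = 176, -1/+1 coding, 5% each: 0.135.
- N = 176, 0/1 coding, outcome scaled to SD 1, 5% each: 0.017, with 85% of the statistics negative.
- N = 176, 0/1 coding, SD 10, 5% each: 0.257.
- N = 126 (63 per group), 0/1 coding, 5% each: 0.476.

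The drop from 0.391 to 0.359 agrees with the formula. Treatment is balanced within strata, so the residual variance, 0.9 x 156.25 = 140.6, replaces SD^2. The shift is then 1.838 + log(140.6 / 44) = 3.000, giving a size of 0.359.

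**The two valid alternatives**, in the same simulations: the LRT with both models refitted by ML rejected in 0.049 to 0.053 of trials, and the F/t test on the REML fit in 0.048 to 0.052. Both are at 5% within simulation error of about 0.005.

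**Transformation.** Section 9.1 permits one, and it would change the outcome scale. As an illustration, assume a log-PCS SD of 12.5 / 37 = 0.34. The shift is then 1.838 - log(44 / 0.114) = -4.12, and the size is about 0.5%.

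**The case against.** The strongest reply is that the protocol never says restricted likelihoods are compared. One sentence concerns estimation and the next concerns testing. REML estimates with an ML-based likelihood ratio test form a standard and valid pair, and the text is compatible with it. The likelihood used, the coding and the software could be settled in a statistical analysis plan, which may exist but is not shown. The 39% also needs 0/1 coding, raw PCS points and the 2*pi constant retained, and the protocol fixes none of these. Finally, the required confidence interval for the treatment contrast would probably expose a gross conflict with the p-value.

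Much of this stands. A reader might infer that the planned test is invalid outright, or that it always inflates the error. The documents support neither: the fault depends on the literal reading, and on a standardised scale the test is conservative. Nor do they support a claim that the treatment estimate is compromised, or that a particular small-sample correction such as Kenward-Roger is needed, since both repairs perform equally well here.

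What does not stand is that this is only detail left for later. The protocol itself fixes both the estimator and the confirmatory test, REML is the only likelihood it names, and the literal combination of the two is the faulty one. A confidence interval reported beside the test does not change which result decides the hypothesis.

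**Conclusion.** The point holds in conditional form. As section 9.1 is worded, the literal procedure is a likelihood ratio test on restricted likelihoods. At N = 176 and SD 12.5 its size at nominal 5% is about 39% (0/1 coding), 15% (-1/+1 coding), 11% (0/1 coding, constant dropped) or 1.6% (0/1 coding, SD units). Allowing 5% of the variance each for centre and setting lowers the 0/1 figure only to about 36%. These sizes rest on the planned N and SD, the assumed variance components, and coding and scale choices that the protocol leaves open.

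If the test uses full-ML fits, its size is about 5% and nothing is wrong except the missing statement. The REML estimate and its standard error are sound under either reading. Because this is the only confirmatory test, and one reading holds the level while the other does not, the sentence should be corrected before outcome data are analysed.

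**What to change.** Keep REML for estimation, and amend the test sentence in section 9.1 to one of the following:

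- the likelihood ratio test for treatment compares the models with and without alpha, both refitted by full maximum likelihood; or
- the contrast alpha_1 - alpha_2 is tested by a t/F test from the REML fit, with a named degrees-of-freedom method and the matching 95% confidence interval.

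Either holds about 5%. The choice between them is one of preference, but it should be made in advance. The second has the convenience that test and interval come from the same fit.

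The cost is one sentence, with no effect on patients, data collection or sample size. Section 9.6 requires deviations from the statistical plan to be described and justified, so settling this now avoids having to defend a change of primary test later.
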